**Methods:**

This study is designed as a community-based, parallel-arm, assessor-blinded randomized controlled trial. Sixty participants were enrolled in this study and randomly assigned to the intervention group (received theory-based sedentary lifestyle change intervention) and the control group (received conventional behavioral change advice). End points were collected at baseline, immediately after the end of the intervention, week 12, and week 18. The primary endpoint is the change in self-reported sedentary time. Secondary endpoints include the changes in step count, time spent in light-intensity physical activity and moderate-to-vigorous-intensity physical activity, Measuring Change in Physical Activity Questionnaire score, Short Physical Performance Battery score, BMI, waist circumference, blood pressure, and Short-Form Health Survey-12-Version 2 score.

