### Study Measurements

#### End Points

The duration of the intervention is 6 weeks with 12 weeks of follow-up. Outcome measures were collected at baseline T1, end of intervention (week 6) T2, week 12 (T3), and week 18 (T4; Figure 2). The primary endpoint is the change in self-reported ST (total ST and SB characteristics, such as screen-based ST, longest continuous ST, and number of sedentary bouts ≤30 min). Secondary endpoints include the changes in step count (steps/d), time spent in LPA (min/wk), time spent in MVPA (min/wk), the Short Physical Performance Battery (SPPB) score, blood pressure, Measuring Change in Physical Activity Questionnaire (MCPAQ) score, waist circumference, BMI, and quality of life (SF-12v2 score) (Table 2).

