### Sample Size Calculation

The sample size was calculated using G*Power software (version 3.1.9.6) [60]. The sample size estimation refers to the standardized deviation of the self-reported ST among community-dwelling older adults obtained from a similar previous study [42]. A total of 48 older adults (24 per group) will be required to detect the effect size of 0.84, with a power of 80% (1−*β*=0.80) and a level of significance of 5% (*α*=.05, 2-tailed) by unpaired *t*-test. Using an SD of 142.98 minutes per day and an expected reduction of 120 minutes per day self-reported sitting time, a sample size of 24 patients per arm is needed. Taking a dropout of 15% into consideration, we will have at least 56 participants in our study.

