### Statistical Analyses

Data analyses follow intention-to-treat principles, using generalized estimating equation models to assess differential changes in the outcome variables between the 2 groups from baseline to 12 weeks (group×time interaction), with adjustment for potential covariates as appropriate (ie, baseline group differences at 2-sided *P*<.25). Effect sizes for continuous outcome variables were estimated using Cohen *d* statistic based on between-group mean differences from baseline T1 to T2, T3, and T4 end points with cutoffs set at 0.2 (small), 0.5 (medium), and 0.8 (large) [62]. Each generalized estimating equation model includes the main effects of group (intervention vs control), time (T2, T3, T4 vs baseline), and 2-way interaction effects (group×time). The group difference in the change from baseline to 6, 12, or 18 weeks between the 2 groups is verified when the 2-way interaction effects (group×time) was statistically significant. All statistical analyses are 2-sided and performed using IBM SPSS 25.0 software. *P* values <.05 is considered statistically significant.

Continuous variables that conform to normal distribution will be expressed as mean (SD) using an independent samples *t* test. Continuous variables that are not normally distributed and ranked variables will use the Mann-Whitney *U* test, expressed as median (M) and quartiles (P₂₅-P₇₅). Categorical table variables will be statistically described by frequency and percentage (%) using *χ*² test or Fisher exact test.

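### The primary outcome is one measure in some places and at least four in others, and the success rule does not fix a week or a single test, so a 5% error rate is not secured

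*Protocol article*

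**What the plan says.** **Measure.** The abstract gives a single quantity: "The primary endpoint is the change in self-reported sedentary time". The Sample Size Calculation section does the same. It plans one unpaired t test at a two-sided 5% level, with "an expected reduction of 120 minutes per day self-reported sitting time" and an SD of 142.98 min/day, and it names no week.

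The End Points section is wider: "The primary endpoint is the change in self-reported ST (total ST and SB characteristics, such as screen-based ST, longest continuous ST", followed by the number of bouts of up to 30 minutes. That is four named measures in an open list. Table 2 also places total sedentary time and the behavior characteristics together under primary outcomes.

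**Time.** Outcomes are collected at baseline and at weeks 6, 12 and 18. The Statistical Analyses section says the models are used "to assess differential changes in the outcome variables between the 2 groups from baseline to 12 weeks". The same paragraph gives the models terms for all three later visits and then states the rule: "The group difference in the change from baseline to 6, 12, or 18 weeks between the 2 groups is verified when" the two-way interaction is statistically significant.

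**Threshold.** P "values <.05 is considered statistically significant" for all analyses. The article names no leading measure or week.

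**The concern.** A reader cannot tell from the article what would count as a positive primary result. The measure is defined in two ways and the time horizon in two ways. The decision rule also leaves open whether the interaction is one test with 3 degrees of freedom or three visit-specific contrasts.

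Under the first option, a significant result shows only that the groups' courses differ somewhere, although the sentence says it verifies a difference at a stated week. Under the second, each measure has three chances to succeed at 5%. Either way, several measures share the label primary, while the sample size allows for one test.

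This matters now because the Results section reports that recruitment and data collection were complete by May 2025. A choice still open at that stage could be made, or appear to have been made, after the results were seen.

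**Working it through.** **1. The plan's own figure.** Inputs from Sample Size Calculation: difference 120 min/day, SD 142.98 min/day, two-sided alpha 0.05, power 80%.
- d = 120 / 142.98 = 0.839.
- Noncentrality for n per group = d × √(n/2). For n = 24 this is 0.839 × √12 = 2.91, and the noncentral t with 46 degrees of freedom gives 81.2% power.
- The stated 24 per group is reproduced, for one test. With all 60 enrolled participants analysed (30 per arm), power is 89.2%.

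**2. Error rate if the tests were independent.** The chance of at least one P<.05 is 1 − 0.95^k.
- k = 3 (one measure, three weeks): 14.3%
- k = 4 (four measures, one test each): 18.5%
- k = 12 (four measures, three weeks): 46.0%

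**3. Allowing for correlation.** The article gives no correlations, so they are assumed. Correlated normal test statistics were simulated (400,000 draws), with correlation 0.3 to 0.9 between weeks and 0.3 to 0.7 between measures. As a check at the enrolled size, t tests on change from baseline were simulated with 30 per arm and equal correlation between visits.

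| Reading of the rule | Chance of at least one P<.05 with no effect |
|---|---|
| Total sedentary time, one 3-df test | about 5% |
| Total sedentary time, three contrasts | about 8–14% (30 per arm: 12–13%) |
| Four measures, one 3-df test each | about 13–19% |
| Four measures, three contrasts each | about 21–42% (30 per arm: about 30–40%) |

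The 30-per-arm ranges are narrow for a structural reason. If all visits are equally correlated at ρ, each change from baseline has variance 2σ²(1 − ρ), and two changes have covariance σ²(1 − ρ). Their correlation is therefore 0.5 whatever ρ is. Varying ρ under that structure tests nothing, so the wider ranges are the fairer statement of uncertainty.

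**4. Cost of keeping every test primary.** Bonferroni, assuming d = 0.839 for every test:

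| Tests | Alpha per test | Power, 24 per arm | Power, 30 per arm | Needed per group for 80% |
|---|---|---|---|---|
| 1 | 0.05 | 81% | 89% | 24 |
| 3 | 0.0167 | 66% | 78% | 32 |
| 4 | 0.0125 | 62% | 75% | 34 |
| 12 | 0.00417 | 47% | 61% | 42 |

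The article does not propose this correction. It shows only that the trial was not sized for several primary tests.

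**The case against.** The strongest reply is that the article describes one model per outcome and a group×time interaction, which can be read as a single 3-df test. If total sedentary time alone was meant as primary, as the abstract and sample size suggest, the error rate is 5% and nothing is inflated. This stands as a possible reading. A reader might infer that any of twelve results can be called a positive trial, or that the 5% level is lost on every interpretation. The text does not support that, because it never says that separate contrasts decide success. Nor does it settle the favorable reading: End Points and Table 2 put the other measures under the primary outcome, and an overall test would not support a claim about week 6, 12 or 18.

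A second reply is that an order of testing or an adjustment may be in a separate analysis plan. That is fair, and its absence here is not the complaint. The complaint is that the article gives two definitions of the measure and two time horizons. A separate plan cannot follow both.

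A reader might also infer that week 12 is the intended primary time point because one analysis sentence names it. That sentence covers all outcome variables and conflicts with the 18-week design given under Study Design and End Points. It may be a slip, so it should not select the week.

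Finally, the simulations use normal statistics or t tests rather than the planned estimating-equation models. They show the size of the problem and are not exact rates.

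**Conclusion.** The concern holds as an inconsistency in what is primary and how it is judged. As written, the rule does not secure a 5% error rate over the primary set. The size depends on the reading, from about 5% (total sedentary time, one overall test) to about 21–42% (four measures by three contrasts), under assumed correlations. On any reading with four primary measures it is at least about 13%. Separately, a significant overall interaction does not establish a difference at a particular week, so the sentence claims more than such a test can show.

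The stated sample size is not wrong. It fits one test of one measure, which is a good reason to define the primary analysis that way. The article does not show whether arm-level data had been examined when it was written, so nothing is concluded about that. The matter should be settled before the results are reported, because it determines what counts as a positive trial.

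**What to change.** - **End Points and Table 2:** name total self-reported sedentary time (min/day) as the only primary measure. Move screen-based time, longest continuous time and bout count to secondary.
- **Statistical Analyses:** reconcile the 12-week and 18-week wording. Replace the sentence on 6, 12 or 18 weeks with one primary test. This can be a single group×time contrast at one named week, or one 3-df interaction test with week-specific contrasts examined only if it is significant.
- **Choice and timing:** the sponsor should choose the week or test, following any earlier prespecification. The trial was registered in March 2024, and that record was not available for this review. The report should say truthfully when the choice was made relative to seeing results by arm.

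The cost is a few sentences and one table edit. With a single contrast, 24 per group and 81% power stand unchanged. With the 3-df test, power depends on the pattern of effects over the three visits, which the article does not give, so it would have to be restated. The real price is that a positive result on another measure or at another week can no longer be called the primary result.

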### Adverse Events and Audit

The research team will collect, report, and assess adverse events to determine their severity and whether they are related to this trial. Serious adverse events and reactions will be reported to the Ethics Committee and appropriate measures will be taken (if present). Audits will be conducted by the School of Nursing, Jilin University.

### Data Collection, Monitoring, Management, and Storage

The principal investigator will input the collected data into a computerized database. Participants’ names will be anonymized and replaced with codes. All other study data will be securely stored on encrypted computer drives in the Research Centre of Jilin University School of Nursing. Only the research team will have access to the data. Data will be securely archived at the end of the study and stored for up to 3 years.

### Ethical Considerations

The design and procedures of this controlled trial followed the Declaration of Helsinki. The study obtained approval from the Ethics Committee of the School of Nursing, Jilin University on December 20, 2023 (grant 2023122001). Written informed consent will be obtained from each participant before baseline measurements. After the follow-up data collection was completed and in accordance with their expressed preferences and needs, participants in the control group were provided with the intervention components and material support they had missed. The study’s implementation adheres strictly to the principles of beneficence, respect for human dignity, justice, and respect for truth and fact.

## Results

The study was initiated in May 2024. As of May 2025, the project had completed participant recruitment (60 participants) and data collection. The final manuscript with findings is expected to be submitted for publication in September 2025. This protocol is published to ensure methodological transparency and to invite peer review focused on study design.

## Discussion

### Anticipated Findings

We hypothesize that community-dwelling older adults receiving the MTM-based stepped intervention for sedentary lifestyle change will demonstrate significantly greater improvements across multiple outcomes compared to those in the conventional health education group. Specifically, the intervention group is anticipated to exhibit a pronounced reduction in total ST, longest continuous ST, and screen-based ST. Concurrently, we expect increases in daily step counts, frequency of sedentary breaks, and time spent in MVPA. These behavioral changes are further projected to translate into meaningful health benefits, including improved quality of life, as well as modest reductions in blood pressure, BMI, and waist circumference.

### Comparison to Previous Work

The evidence indicates that older adults spend approximately 65% to 80% of their waking hours sedentary [63]. In a survey of Chinese older adults, 26.1% participated in regular PA (more than 3 times a week, each time for more than 30 min of MVPA) [64], suggesting that sedentary lifestyles may be prevalent among older adults. The long-term presence of low energy expenditure during waking hours is detrimental to physical health, mental health, and quality of life and exacerbates the adverse outcomes [36]. Therefore, interventions targeting changes in sedentary lifestyles are necessary to improve health outcomes in older adults. Previous research has confirmed the separate benefits of reducing SB and increasing PA. However, the feasibility and efficacy of a comprehensive, stepped intervention that systematically integrates both strategies to modify sedentary lifestyles in older adults have not been adequately examined.

Most current interventions for PI in older adults involve the traditional “elevator approach,” that is, interventions aimed directly at increasing PA, and tend to ignore the potential SB of the target population [41]. Despite increased PA, older adults may still engage in SB [65,66]. As the health effects of SB are independent of PA, too much cumulative SB can still harm overall health and make it difficult to produce the desired health benefits [67,68]. Similarly, modifying SB alone—without emphasizing the quantity of MVPA—the presence of PI still leads to an inability to efficiently achieve the desired health benefits [36]. Our study addresses this critical gap by proposing an integrated, staircase approach-based sedentary lifestyle intervention that simultaneously targets SB reduction and PA promotion, guided by the MTM.

The MTM suggests that for initiation of behavior change, individuals perceive that the advantages of behavior change outweigh the disadvantages, and they have behavioral self-confidence and are supported by the physical environment. To maintain behavior change, it is necessary to translate one’s feelings into goals, to constantly strive for change, and to have the support of the social environment [45]. Rather than simply applying behavioral change theory, our approach was informed by the specific characteristics of the older adults (eg, cognition, environment, social norms), leading to a targeted selection of components and design of strategies. According to qualitative studies, older adults are often unaware of the benefits of reducing SB, resulting in low self-efficacy [69,70]. Therefore, there is a need to provide knowledge-based sessions on SB for older adults, emphasizing its advantages and disadvantages and the importance of behavioral change and offering practical tools [43]. For instance, the cube timer was selected as a tool to interrupt SB. Interventions aimed at breaking up ST through standing and LPA throughout the day may be an effective and more feasible option for improving health [42,71]. This initial step within the staircase approach laid the foundation for subsequently introducing higher-intensity PA, thereby demonstrating a systematic implementation that transcends previously fragmented applications. Higher daily step counts are associated with higher LPA or SB ratios and greater time spent on MVPA [72]. This study also added a pedometer-based intervention that included sessions on the benefits of walking and recommendations for self-monitoring daily steps with a pedometer. Pedometer and cube timer serve as low-technological-threshold, cost-efficient tools that may present a pragmatic alternative to many digital interventions by overcoming the technological usage barriers commonly encountered by older adults [43].

Distinct from prior research predominantly focused on individual-level behavior change, this study also specifically focuses on the impact of sociocultural environments on SB in older adults. Consequently, our intervention design incorporates components aimed at mobilizing social support to address this documented, yet frequently overlooked challenge in existing interventions. Existing sociocultural expectations and social norms are supportive of older adults’ seated position, considering it “safe” for them, and supporting their inactivity as a “benevolent” act or, in some settings, standing up and moving around when everyone is sitting is considered “embarrassing” behavior [28,69,73]. These viewpoints may hinder older adults’ capacity to change their SB in community settings. Therefore, our intervention integrates strategies to engage participants’ close social networks and community members, creating a supportive environment that aligns with the changes in the social environment construct of the MTM.

### Strengths and Limitations

This research has several strengths. First, our study takes community-dwelling older adults as the research population; applying a sedentary lifestyle modification intervention program based on the MTM model, and through the chosen behavior-change techniques, acting on the participants’ behavior, physical and social environments, addresses the problems of difficulty in breaking habitual SB and low adherence to behavioral modification and ultimately achieves the gradual transformation of SB into PA of different intensities and long-term maintenance of behavioral change. Second, this study uses the “staircase approach” as an activity intensity gradient for modifying sedentary lifestyles. It facilitates a transition from SBs to standing and light activities, then to LPA, and further to MVPA, ultimately establishing a sustainable behavior change model that delivers health benefits. The program provides community-dwelling older adults with sedentary lifestyles a personalized behavior change program that is easier to adhere to and better suited to their daily activity patterns.

There are also several limitations. The modest sample size in this study may constrain the generalizability and statistical power of the outcomes. Moreover, the reliance on self-reported measures for SB introduces potential recall bias. Future investigations should utilize objective monitoring devices, such as accelerometers, to enhance data accuracy and adopt multicenter designs with larger cohorts to validate the external validity of the findings. Extending both the intervention and follow-up durations is also recommended to better evaluate the long-term sustainability of the intervention effects.

### Future Directions

This study offers valuable practical implications for nursing practice in health management of community-dwelling older adults. For older adults with sedentary lifestyles, the MTM-based stepped intervention demonstrates potential in systematically reducing SB and promoting MVPA through a progressive intensity gradient, thereby facilitating health benefits. It is recommended that community health centers incorporating such interventions into routine health management programs, promoting the use of low-cost prompting tools (eg, cube timer), combined with personalized goal-setting and social support, is essential to enhance participant engagement and adherence. Furthermore, future initiatives may explore the integration of digital tools (eg, mobile app reminders) with the stepped intervention model to improve both the accessibility and scalability of the intervention.

### Dissemination

Participants will be informed of the results of the study through a summary report. Study results will be disseminated through journal publications. The anonymized participant dataset will be retained in an appropriate data archive for 3 years after the study’s end for sharing. Without participant approval, the results of this study and any information submitted by participants will not be disclosed to any third party.
